### Informed consent and ethical approval

All eligible patients are informed about this study and given the time they needed to consider participation. The investigator of this study and an independent physician not involved in the study may be approached for questions. Patients who are willing to participate sign an informed consent form. This study has been approved by the medical ethical review board of the Radboud University Medical Centre, Nijmegen (registration number: 2012/233), and is registered in The Netherlands National Trial Register (registration number: NTR3527).

### Intervention

The intervention consists of geriatric physiotherapy according to the Coach2Move strategy ([see Additional file 1 and Table 1]). The Coach2Move strategy helps the GPT in clinical reasoning by providing an extensive, pre-structured and systematically organized diagnostic protocol. For the diagnostic phase of the Coach2Move strategy more time (1.5 hours) is available than for the conventional physiotherapy intake (30 minutes). Impairments and disabilities, but also possibilities, wishes, barriers and facilitators relevant to physical functioning are thoroughly examined. Motivational interviewing is used to find and deal with the barriers to individuals becoming physically active, but also to find out what personal goals a patient wants to achieve. Physiotherapy treatment in the Coach2Move strategy is focused on increasing motivation to be physically active by working on personal goals and removing physical barriers. Using shared decision making together with the patient, the GPT sets SMART goals – specific, measurable, acceptable, realistic and (with a) timeline. The GPT coaches the patient in reaching and maintaining his/her own goals (self-management) using appropriate feedback.

**Table 1 T1:** The innovative elements of the Coach2Move strategy

**The innovative elements of the Coach2Move strategy**	
1	Use of motivational interviewing: exploring questions for help and barriers and facilitators in relation to physical activity.
2	Use of an algorithm (HOAC-II*^a^) that emphasizes an extensive intake and supports clinical reasoning in order to set priorities.
3	Shared decision making on meaningful treatment goals to increase physical activity.
4	Coaching on self-management to increase long-term results.
5	Focusing on meaningful activities at home with help from family, friends or professionals.
6	Working according to three patient-tailored intervention profiles with a predefined number of sessions.

^a^HOAC, Hypothesis Oriented Algorithm for Clinicians.

In Coach2Move, three intervention profiles with a predefined number of sessions can be chosen. Patients are categorized into one of these three profiles based on the complexity of their problems and their potential for improvement. The first profile deals with patients who do not need physiotherapy intervention on the level of body function or structure, but who just need coaching and advice (≤4 sessions). The second profile is aimed at improving functions, abilities and activities over a course of seven to nine sessions for patients who need temporary treatment to overcome barriers to becoming physically active. In the third profile, patients with specific problems in participation, activities and functions are treated and coached in 12 to 18 sessions.

GPTs are trained in the Coach2Move strategy in a basic training of two days. This training focuses on:–

1. Clinical reasoning.

2. Using appropriate measurement instruments in the diagnostic phase but also in the evaluation of the intervention and as feedback instrument for the patient and therapist.

3. Shared decision making.

4. SMART focused goals (specific, measurable, acceptable, realistic, timeline).

5. Learning to focus on coaching and self-management.

6. Learning to work in a patient-centered way and using measurements for feedback.

7. Learning motivational interviewing skills.

8. Learning skills for adequate coordination with other formal and informal caregivers involved.

In this study, the control intervention consists of conventional physiotherapy provided by a PT. A one-day basic training is organized for the PTs to enhance their motivation to participate in this RCT. The training consists of general information regarding the treatment of older adults. In this training, no attention is paid to clinical reasoning, measurement instruments, shared decision making, motivational interviewing or self-management.

The treatment delivered by both the GPTs and the PTs consists of conventional physiotherapy modalities such as training activities in daily living, balance and muscle strength. No standardized intervention is prescribed and in both groups the physiotherapist is free to determine the appropriate intervention and level to reach the intervention goals. We expect less focus on physical activity in the control group. Moreover, the control group can freely decide how many sessions are needed. This is standard procedure in physiotherapy care in the Netherlands.

The key elements of the Coach2Move strategy are set out in Table 1 and these are the main distinguishing factors between the intervention and the control group. Even though shared decision making, patient-centered treatment and goal setting on participation level are considered important, physiotherapists have difficulty actually applying this in clinical practice [18-20]. The Coach2Move strategy offers education in these elements and supports physiotherapists during the implementation, which we expect to result in a contrast between the intervention and control groups. Both therapies are expected to be effective; however, we hypothesize that the Coach2Move strategy will be more effective on the level of physical activity and in reaching treatment goals in fewer physiotherapy sessions.

### Study parameters

The main study parameter is the level of physical activity during follow-up over six months. The level of physical activity will be measured using the LASA Physical Activity Questionnaire (LAPAQ) [21]. The LAPAQ is a reliable and valid instrument specifically developed for older adults. The LAPAQ is a comprehensive questionnaire on diverse (physical) activities of daily living including walking, riding a bicycle, gardening, light household chores, heavy household chores and sporting activities. Based on the results of this questionnaire, the average amount of physical activity in minutes per day and minutes per week can be assessed.

Secondary study parameters include mobility, quality of life, level of frailty, fatigue and perceived effect. Mobility is measured using the ‘get up and go’ test (GUG) [22], the six-minute walking test (6MWT) [23] and walking speed (WS) timed over a 10-meter distance [24]. During the modified GUG, the patient is instructed to rise out of a chair and walk 10 meters [24]. This procedure is timed and the duration in seconds is the score for this test. The effort of completing the same test is measured using the BORG scale of perceived exertion [25]. The Borg scale ranges from 6 to 20, where 6 indicates no exertion and 20 the highest possible exertion. The 6MWT consists of six minutes walking at the patients’ self-determined pace. The score on this test is the distance in meters covered in six minutes. WS is timed on a 10-meter distance. The mean time in seconds it takes the patient to walk this distance (at his/her own preferred speed) over three tries, is the final score on this test [24]. The SF-36 is used as a measure of quality of life [26]. The SF-36 is a 36-item questionnaire on health status. Questions relate to eight domains: vitality, physical functioning, bodily pain, general health perceptions, physical role functioning, emotional role functioning, social role functioning and mental health. Each domain is equally weighted and a standardized scoring system results in two scores: a physical score and a mental/emotional score. Both scores range from 0 to 100 with an average score of 50, and a higher score indicating a better quality of life.

To measure the level of frailty, the Evaluative Frailty Index for Physical activity (EFIP) is used [14]. The EFIP is a 50-item questionnaire based on deficit accumulation (symptoms, signs, disabilities) in multiple domains (physical, psychological, social and general health status). The score on this questionnaire is expressed as the ratio of deficits present to the total number of deficits considered. The score ranges from 0 to 1, with 0 indicating no frailty and 1 indicating maximum frailty.

Fatigue is measured using the Numeric Rating Scale (NRS)-fatigue [27], which is a scale from 0 to 10 in which the patient can indicate what level of fatigue is experienced. A score of 0 represents no fatigue at all and a score of 10 represents the most possible fatigue.

Perceived effect is measured with the PSC (patient specific complaints) questionnaire and Global Perceived Effect (GPE). The PSC is an instrument in which patients can determine three activities in which they experience the most trouble [28]. For each activity one can judge the level of experienced trouble on a scale from 0 to 10 in which 0 indicates no trouble at all and 10 indicates that the activity cannot be performed. The Global Perceived Effect (GPE) [29] score is used to measure the patient’s opinion about the effect of the intervention on a nine-point scale ranging from very much improvement to very much deterioration.

Co-morbidity is registered using the Cumulative Illness Rating Scale-Geriatrics (CIRS-G) [30]. The CIRS-G in combination with registration of the physiotherapy intervention during each session and registration of health care utilization will be used to explore whether a physiotherapy intervention is adjusted because of the presence of co-morbidity, if the presence of co-morbidity influences the effect of an intervention, and if co-morbidity brings about interventions other than physiotherapy.

Health care utilization is registered by means of a questionnaire. The questionnaire considers the type and number of medical consultations, medication use, hospital stay, nursing home stay, use of residential facilities, professional home care and the purchase of assistive devices in the three months before the questionnaire is taken.

### Patient flow

Figure 1 describes the patient flow. This RCT has an inclusion period of 15 months and a follow-up of six months. This means that the RCT will be completed in 21 months. Patient recruitment started in September 2012 and will end in November 2013.

**Figure 1 F1:**
[figure not shown]
**Patient flow.** CIRS-G, cumulative illness rating scale for geriatrics; EFIP, evaluative frailty index for physical activity; GPE, global perceived effect; GPT, geriatric physical therapist; LAPAQ, LASA physical activity questionnaire; modified GUG, modified get up & go test; NRS fatigue, numeric rating scale fatigue, PSC, patient specific complaints; PT, physiotherapist; SF-36, short form 36; WS, walking speed; 6MWT, 6 minute walking test.

### Sample size

To calculate the sample size, we use the formula for an ANCOVA, derived by Teerenstra *et al*., which states that the sample size uncorrected for clustering and baseline measurement has to be multiplied by two factors [31]. First, a factor that accounts for the clustering: DE = (1 + (n-1) *ICC), where n is the average number of patients per therapist and ICC is the intra-cluster correlation of patients within a therapist. Second, a factor that accounts for the adjustment for baseline: (1-r^2^) with r = r_c*(n*ICC/DE) + r_s*((1-ICC)/DE), where r_c is the autocorrelation and r_s is the autocorrelation of patients. The autocorrelation is the correlation between the three-month measurement and baseline measurement.

#### *Uncorrected sample size*

In our pilot study of ten patients treated by one of two therapists, we found on log scale an increase of 1.21 from baseline and a standard deviation of 1.0 (in the pre-intervention scores). This corresponds to a 3.35 fold increase from baseline scores on the untransformed LAPAQ scale. The control group in our study is comparable to the experimental group in the study performed by Rubenstein *et al*., which found a 20% increase from baseline (1.2-fold increase) [32]. Thus the intervention is estimated to be 3.35/1.2 = 2.8 times as effective as the control treatment. To account for possible overestimation of the effect by the pilot study and possible contamination, we assume that at least 60% of this effect will be retained; that is, the intervention is at least 1.68 times as effective as the control. Then, the effect on log scale is 0.5 (sd = 1.0 as above). The uncorrected sample size to detect this difference with 80% at a significance level of 0.05 is 64 patients per group.

#### *Adjustment for baseline*

From our pilot study we estimated a subject-autocorrelation r_s = 0.73; therapist-autocorrelation could not be estimated (too few therapists), but conservatively we set it to be moderate r_c = 0.4. Then r = 0.6 and the correction for baseline adjustment is 1-(0.6^2^) = 0.64.

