#### *Clustering*

In our pilot study we found ICC = 0 and, conservatively setting the ICC = 0.05, the correction for clustering is 1 + (n-1)*0.05. Allowing for maximal 20% dropout, the corrected sample size can be calculated with: 64*0.64*(1 + (n-1)*0.05)* 1/(80%). Table 2 gives the sample sizes when a different number of physiotherapy practices are included. If each participating physiotherapist (2 per practice, 13 practices = 26 physiotherapists, 12 physiotherapists per group) were to treat 5 patients, a total number of 130 patients would be included (65 patients per group). This is more than the 62 patients per group necessary according to the power calculation (see Table 1). If each therapist were to treat four patients, however, the power would not be reached. Therefore we will include 65 patients per group (total = 130) in this trial.

**Table 2 T2:** Sample size calculation

**n = Number of patients per cluster**	**Sample size per group: 64*0.64*(1 + (n-1)*0.05)* 1/(80%)**	**#Clusters group: sample size /n**
10	75	8
9	72	8
8	70	9
7	67	10
6	64	11
5	62	13
4	59	15

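### The baseline correlation r = 0.6 does not follow from the plan's own formula (0.66 at five patients per therapist), so Table 2 and the rejection of four patients per therapist do not stand as written

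*Protocol article*

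**What the plan says.** The Sample size section multiplies an uncorrected sample size by two factors. The first is the design effect, "DE = (1 + (n-1) *ICC), where n is the average number of patients per therapist". The second is 1 − r², with r defined (closing bracket omitted here) as "r = r_c*(n*ICC/DE) + r_s*((1-ICC)/DE". By this definition r changes with n.

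The inputs are spread over three subsections:

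- Uncorrected sample size: "Then, the effect on log scale is 0.5 (sd = 1.0 as above"), and the number needed "to detect this difference with 80% at a significance level of 0.05 is 64 patients per group".
- Adjustment for baseline: "we estimated a subject-autocorrelation r_s = 0.73"; the therapist autocorrelation r_c is set at 0.4 and labelled conservative. The text continues: "Then r = 0.6 and the correction for baseline adjustment is" 0.64. It does not say which n was used or that r was rounded down.
- Clustering: ICC set at 0.05, also labelled conservative; dropout of at most 20%; 13 practices with two therapists each.

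Table 2 applies the fixed factor 0.64 for n from 10 down to 4 and arrives at 62 per group for n = 5 and 59 for n = 4. The text below concludes "If each therapist were to treat four patients, however, the power would not be reached" and on that ground sets 65 per group, 130 in total. It also describes the therapists as "26 physiotherapists, 12 physiotherapists per group".

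**The concern.** The value 0.6 is presented as the result of putting the stated inputs into the stated formula, and it is not. Because r depends on n, no single factor can serve all rows of Table 2 in any case. The gap is widest at small n, which is where the choice between four and five patients per therapist is made.

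That choice is the difference between 104 patients (2 × 13 × 4) and 130 (2 × 13 × 5), and the article justifies it only by the claim that four would fall short. If the claim does not follow from the plan's inputs, the sample size has no correct stated justification, even if 130 is a sensible number. The miscount of therapists in the same paragraph adds to this: 12 therapists with five patients each give 60, below the plan's own 62.

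**Working it through.** **Inputs.** Effect 0.5 and SD 1.0 on the log scale, 80% power, alpha 0.05 (Uncorrected sample size); r_s = 0.73 and r_c = 0.4 (Adjustment for baseline); ICC = 0.05, 20% dropout, 26 therapists (Clustering). The article does not say whether alpha is one- or two-sided; two-sided is assumed because it reproduces the 64.

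**Step 1: the plan's own figures.** A two-sample t-test with effect 0.5, SD 1, two-sided 0.05 and 80% power needs 63.8, so 64 per group reproduces. With the fixed factor, 64 × 0.64 × DE / 0.8 gives 61.44 at n = 5 and 58.88 at n = 4. Rounded up these are 62 and 59, and the other five rows reproduce in the same way. The only fault in the chain is r.

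**Step 2: r from the stated formula.** DE = 1 + (n − 1) × 0.05.

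- n = 5: DE = 1.20; r = 0.4 × (0.25/1.20) + 0.73 × (0.95/1.20) = 0.083 + 0.578 = 0.661; 1 − r² = 0.563.
- n = 4: DE = 1.15; r = 0.4 × (0.20/1.15) + 0.73 × (0.95/1.15) = 0.070 + 0.603 = 0.673; 1 − r² = 0.548.

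Solving for r = 0.6 gives n = 12.35. At n = 5, r = 0.6 would need r_c = 0.106 or ICC = 0.115 instead of the stated values.

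**Step 3: Table 2 recomputed** as 64 × (1 − r²) × DE / 0.8, rounded up as the plan does. Clusters are the recomputed size divided by n, rounded up.

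| n | r | 1 − r² | Stated per group | Recomputed per group | Stated clusters | Recomputed clusters |
|---|---|---|---|---|---|---|
| 10 | 0.616 | 0.620 | 75 | 72 | 8 | 8 |
| 9 | 0.624 | 0.611 | 72 | 69 | 8 | 8 |
| 8 | 0.632 | 0.600 | 70 | 65 | 9 | 9 |
| 7 | 0.641 | 0.589 | 67 | 62 | 10 | 9 |
| 6 | 0.651 | 0.577 | 64 | 58 | 11 | 10 |
| 5 | 0.661 | 0.563 | 62 | 55 | 13 | 11 |
| 4 | 0.673 | 0.548 | 59 | 51 | 15 | 13 |

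The unrounded values in the last two rows are 54.02 and 50.38.

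**Step 4: therapists.** 26/2 = 13 per group, which agrees with 65 = 13 × 5 and with the 13 clusters that Table 2 lists at n = 5. Four patients each give 13 × 4 = 52, at or above the 51 required.

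**Step 5: power.** Effective size per group is E = 0.8 × N / (DE × (1 − r²)); power = Φ(0.5 × √(E/2) − 1.96).

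| Randomised per group | r from the formula | r = 0.6 |
|---|---|---|
| 65 (13 × 5) | E = 77.0, power 87% | E = 67.7, power 83% |
| 52 (13 × 4) | E = 66.1, power 82% | E = 56.5, power 76% |
| 60 (12 × 5) | E = 71.1, power 85% | E = 62.5, power 80% (79.8%) |
| 48 (12 × 4) | E = 61.0, power 79% | E = 52.2, power 72% |

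Using the t distribution lowers these by about half a percentage point to one point.

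**The case against.** The best defence is that 0.6 is a cautious round figure. It lies below the formula value in every row (0.616 to 0.673), so 0.64 is an upper bound on 1 − r² over the whole table, and the required sample is overstated, never understated. The plan is cautious elsewhere, in r_c and in the ICC. Caution about r_s would also be reasonable, since it comes from ten pilot patients: a rough Fisher-z 95% interval around 0.73 runs from about 0.19 to 0.93, and r = 0.6 at n = 5 corresponds to r_s of about 0.65, a modest discount.

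The reversal at n = 4 is also thin. It has one patient per group to spare, it fails if r_s is below about 0.714, and it needs 13 therapists per group; with 12, 48 patients fall short of 51. Finally, the 12 is plainly a slip, since the surrounding figures all imply 13.

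Most of this stands as a description of consequences: the direction is safe, recruitment is not endangered, and the article states no numerical power at 65 per group, only the 80% target and, under Statistical analysis, a claim of more than 80%, which holds either way.

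It does not rescue the text. The article labels its cautious choices for r_c and the ICC as such, but introduces 0.6 as a derived value. Ordinary rounding does not explain it either: in the rows for n = 4, 5 and 6, r rounds to 0.7. The thin margin at n = 4 would be a good reason to prefer five patients per therapist, but it is not the reason given.

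**Conclusion.** The concern holds. Under the plan's own formula and inputs, r is 0.661 at n = 5, the baseline factor is 0.563 rather than 0.64, and the requirement is 55 per group rather than 62. All seven rows of Table 2 are too high by 3 to 8 patients, through this one input. The sentence rejecting four patients per therapist is wrong under the plan's own rule: 51 are needed and 52 are available, with power of about 82%.

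The error overstates the requirement, so the planned 65 per group is more than adequate, at about 87% power under the baseline-adjusted comparison with 20% dropout. These figures rest on two-sided alpha, 13 therapists per group, and the stated r_s, r_c and ICC taken at face value. The conclusion on four patients is sensitive to r_s and to the number of therapists; the mismatch between formula and stated r is not. This should be corrected because the published justification for the sample size does not reproduce, not because the trial is too small.

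**What to change.** Choose one of two routes and state it:

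1. Compute r separately for each n, replace both result columns of Table 2 with the recomputed values, give the requirement at n = 5 as 55 per group, and remove or correct the sentence on four patients per therapist.
2. Keep r = 0.6, but declare it a deliberate value below the formula result, chosen because r_s comes from ten pilot patients, and say that the patients beyond the formula requirement are reserve. The sentence on four patients should then be tied to that cautious assumption.

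Under either route, correct 12 therapists per group to 13, and give the power at 65 per group: about 87% with r from the formula, 83% with r = 0.6. If the choice of five patients per therapist is kept, justify it by the one-patient margin at four and the uncertainty in r_s.

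The cost is a text and table correction. Enrolment can stay at 130, and neither recruitment nor the analysis changes.

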#### *Clustering*

In our pilot study we found ICC = 0 and, conservatively setting the ICC = 0.05, the correction for clustering is 1 + (n-1)*0.05. Allowing for maximal 20% dropout, the corrected sample size can be calculated with: 64*0.64*(1 + (n-1)*0.05)* 1/(80%). Table 2 gives the sample sizes when a different number of physiotherapy practices are included. If each participating physiotherapist (2 per practice, 13 practices = 26 physiotherapists, 12 physiotherapists per group) were to treat 5 patients, a total number of 130 patients would be included (65 patients per group). This is more than the 62 patients per group necessary according to the power calculation (see Table 1). If each therapist were to treat four patients, however, the power would not be reached. Therefore we will include 65 patients per group (total = 130) in this trial.

**Table 2 T2:** Sample size calculation

**n = Number of patients per cluster**	**Sample size per group: 64*0.64*(1 + (n-1)*0.05)* 1/(80%)**	**#Clusters group: sample size /n**
10	75	8
9	72	8
8	70	9
7	67	10
6	64	11
5	62	13
4	59	15

### Statistical analysis

Descriptive statistics will be used to present group characteristics on age, education, marital status, multi-morbidity, level of frailty, number of post-operative patients, therapy adherence and adverse effects. Any asymmetry between the intervention and control group on these variables at baseline will be statistically corrected. The effects of the intervention are analyzed according to the intention-to-treat principle. The analysis of the primary and secondary outcome measures employed a linear mixed model to relate the three- and six-month outcomes to the effect of the treatment. Therapist is taken as a random effect in this model to account for the clustering of patients with therapists. Measurement (baseline, 3 months, 6 months) is included as a random effect to account for correlation of measurements over time. Because this analysis uses all three measurements (baseline, 3 and 6 months), it will actually be more powerful than an ANCOVA analysis and the power of the study will be more than 80%.

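### A random effect for measurement occasion does not model correlation within a patient, and no patient term is named; followed literally, a test of change from baseline would have a standard error about 1.5 times too large

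*Protocol article*

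**What the plan says.** The Statistical analysis section states that the analysis of primary and secondary outcomes "employed a linear mixed model to relate the three- and six-month outcomes to the effect of the treatment". It names two random effects. The first is therapist: "Therapist is taken as a random effect in this model to account for the clustering of patients with therapists". The second is occasion: "Measurement (baseline, 3 months, 6 months) is included as a random effect to account for correlation of measurements over time". Neither this section nor any other names a patient random effect or a within-patient covariance structure.

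The same section argues that, because baseline, three-month and six-month values are all used, "it will actually be more powerful than an ANCOVA analysis and the power of the study will be more than 80" per cent.

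The sample size sections do separate patient from therapist correlation. Under Adjustment for baseline: "From our pilot study we estimated a subject-autocorrelation r_s = 0.73", and for therapists, "conservatively we set it to be moderate r_c = 0.4". Under Clustering, the ICC is fixed by "conservatively setting the ICC = 0.05".

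**The concern.** The sentence gives the occasion effect a job it cannot do. A random effect for a three-level visit factor is one draw per visit, shared by everyone measured then. It correlates different patients at the same visit, leaves one patient's own values uncorrelated, and cancels from any comparison of arms. The three visits are also chosen design points, and three levels hardly identify a variance.

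That leaves the therapist intercept, which cancels from change over time. A contrast of change is therefore judged against a residual that still contains most of the variance between patients, although the sample size counts on much of that variance being removed. The gain in precision claimed for using all three measurements exists only if the correlation within patients is modelled. The sentence governs the primary and every secondary outcome, so an analyst who follows it could lose power that the trial was sized to have.

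**Working it through.** **Inputs from the article.** Effect 0.5 and SD 1.0 on the log scale (Uncorrected sample size). Within-patient correlation r_s = 0.73 and therapist autocorrelation r_c = 0.4 (Adjustment for baseline). ICC 0.05, 13 therapists per arm, 5 patients each, at most 20% dropout (Clustering). My assumption: the correlation is the same between every pair of visits.

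**The plan's own figure.** 64 × 0.64 × (1 + 4 × 0.05) / 0.80 = 61.44, rounded up to 62 per group, as in Table 2. The article states: "Then r = 0.6 and the correction for baseline adjustment is" 0.64. Its own formula at n = 5 gives r = 0.4 × (0.25/1.2) + 0.73 × (0.95/1.2) = 0.66, so 0.6 is on the cautious side. The sample size is not in question here.

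**Contrast examined.** Between-arm difference in (mean of 3 and 6 months minus baseline). The variance multiplier is 1 + 1/2 = 1.5 per arm, or 3 for two arms.

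**Correct SE, n = 5 per therapist.**
- Visit-specific variance per observation: n·ICC·(1 − r_c) + (1 − ICC)(1 − r_s) = 5 × 0.05 × 0.6 + 0.95 × 0.27 = 0.4065.
- SE = √(3 × 0.4065 / 65) = 0.137.

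**SE reported by the model as written, n = 5.** With a therapist intercept, a shared visit effect and independent residuals, the residual pools two sources:
- patients within therapist-by-visit cells: 78 × 4 = 312 df, variance 0.95;
- therapist-by-visit within arm: 24 × 2 = 48 df, variance 0.4065.

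Residual variance = (312 × 0.95 + 48 × 0.4065) / 360 = 0.878. SE = √(3 × 0.878 / 65) = 0.201. Ratio 0.201 / 0.137 = 1.47.

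**Consequences (normal approximation), n = 5.** True type I error = 2 × [1 − Φ(1.96 × 1.47)] ≈ 0.004. Power = Φ[(0.5 − 1.96 × 0.201) / 0.137] ≈ 78%. With a correct SE it is Φ(0.5 / 0.137 − 1.96) ≈ 95%.

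**Other settings.**

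| Patients per therapist | ICC | r_s | Model SE | Correct SE | Ratio | Power as written | Power with correct SE |
|---|---|---|---|---|---|---|---|
| 5 | 0.05 | 0.73 | 0.201 | 0.137 | 1.47 | 78% | 95% |
| 4 (20% dropout) | 0.05 | 0.73 | 0.222 | 0.147 | 1.50 | 67% | 92% |
| 5 | 0.05 | 0.6 | 0.203 | 0.156 | 1.30 | 74% | 89% |
| 5 | 0.05 | 0.4 | 0.206 | 0.182 | 1.13 | 70% | 78% |
| 5 | 0 | 0.73 | 0.204 | 0.112 | 1.83 | 82% | 99% |

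**Simulation check.** A small REML simulation of the first row (53 runs) gave a mean model SE of 0.202 against an empirical SD of 0.140, in line with the closed form.

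**The other contrast.** I also simulated an arm effect on the two follow-up scores with baseline as covariate and a therapist intercept only (148 runs). Mean SE was 0.126 against an empirical SD of 0.117, with type I error 4.7%. Therapists are nested in arm, so the therapist intercept absorbs the patient variance and the SE is about right.

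**The case against.** The strongest reply is that the article never names change from baseline, or group by time, as its test. It relates the follow-up outcomes to treatment, and Study parameters defines the main parameter as activity level during follow-up. On that reading, with baseline adjustment, the SE is about right even without a patient term. This stands: the inflation belongs to one plausible contrast, not to every reading of the model.

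Second, the sentence may be shorthand for measurements repeated within patient. Its stated purpose and the separate patient and therapist correlations in the sample size point that way, and a condensed article may leave nesting to a fuller document. If so, the inflation shown here disappears. That also stands, but it does not repair the text: the model that is stated cannot do what the sentence claims for it.

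Third, the size depends on assumptions. With r_s = 0.4 the ratio is only 1.13, and there a correct SE would itself give just 78% power. With ICC = 0 and 5 patients per therapist, power as written is about 82%, so the shortfall is not universal.

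A reader might infer more: that the primary result will have a wrong SE whatever the contrast, that false positives are inflated, or that treatment by time cannot be tested. The article supports none of these. The contrast is left open, the error where it arises is conservative, and a treatment-by-time term is simply not specified.

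**Conclusion.** The specification is wrong as stated: a shared occasion effect cannot carry within-patient correlation, and no patient term is named. The numerical harm is conditional. It arises if the model is fitted literally and treatment is tested as a difference in change. With the plan's own inputs and equal correlation between visits, the SE is then about 1.5 times too large, and power is about 78% with full retention or 67% after 20% dropout, against the claim of more than 80%. The risk is a missed effect, not a false positive. The document cannot show which model would be fitted, so it does not support concluding that the analysis will in fact ignore patient correlation. It does justify correcting the sentence, and the power claim that leans on it, before the data are analysed.

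**What to change.** Replace the sentence on measurement. Enter measurement as a fixed effect with a treatment-by-measurement term, and state which contrast is the primary test. Model the repeated values with a patient random intercept or an unstructured within-patient covariance, and keep therapist as a random effect.

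One detail matters when doing so. The plan's r_c = 0.4 means therapist effects differ between visits, and baseline is taken before allocation. The therapist effect should therefore act on the follow-up scores or be allowed to vary by visit. With only constant patient and therapist intercepts, the residual at n = 5 would be (208 × 0.2565 + 48 × 0.4065) / 256 = 0.285 and the SE √(3 × 0.285 / 65) = 0.115, below the correct 0.137.

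Then restate the power claim for that model and contrast, or drop it. The cost is a few sentences of analysis text and standard mixed-model software, with no change to data collection or sample size.
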